# Antioxidant dressing therapy versus standard wound care in chronic wounds (the REOX study): study protocol for a randomized controlled trial

**DOI:** 10.1186/s13063-020-04445-5

**Published:** 2020-06-08

**Keywords:** Chronic wound, Wound healing, Hard-to-heal wounds, Antioxidant dressing, Oxidative stress

## Abstract

**Background:**

A wound that does not heal in the orderly stages of the healing process or does not heal within 3 months is considered a chronic wound. Wound healing is impaired when the wound remains in the inflammatory stage for too long. A range of factors can delay the healing process: imbalance between proteases and protease inhibitors in the wound bed; bacterial colonization and the presence of biofilm; and oxidative stress. Recently, wound management has improved significantly. A new antioxidant dressing has been developed, which combines an absorbent matrix obtained from locust bean gum galactomannan and a hydration solution with curcumin and N-acetylcysteine. This dressing combines the advantages of moist healing in exudate management and free radical neutralization, achieving wound reactivation. The primary aim of this study is to compare the effect of the antioxidant dressing on chronic wound healing against the use of a standard wound dressing in patients with hard-to-heal wounds.

**Methods:**

We will conduct a multicentre, single-blind, randomized controlled trial with parallel groups. Participants will be selected from three primary public health care centres located in Andalucía (southern Spain). Patients will be randomized into an intervention group (antioxidant dressing) or a control group (standard wound dressing). Assessments will be carried out at weeks 2, 4, 6 and 8. Follow-up will be for a period of 8 weeks or until complete healing if this occurs earlier.

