### Randomization and blinding

Patients (*n* = 54) will be randomized into an intervention group (antioxidant dressing) or control group (standard clinical practice using dressings that create a moist environment). The block randomization scheme was generated using the EPIDAT software. Participants will be randomized to receive antioxidant dressing or standard wound dressing with a 1:1 allocation ratio (Fig. 2) using stratified block randomization with a fixed block size per centre. Once the patient has agreed to participate and has been shown to meet the inclusion criteria, the clinical nurse will open opaque closed envelopes sequentially numbered containing a sheet (folded four times) with the group allocation. Neither the patient nor the clinical nurse is blinded to the treatment received; the data and the wound pictures will be codified and the assessor who evaluates the wound pictures and the data analyst will be blinded to the treatment.

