### Data collection and management

Participants eligible for study entry will be given a unique, sequential, centre-specific study identifier. Clinical data will be entered into paper-based case report forms. After each assessment, the data will be handled according to internal procedures and stored in a secure server. These files will be backed-up into a password-protected environment. Hard copies will be stored locally, in compliance with the Spanish Data Protection Law (2018).

Each patient included in the study will be assessed by one clinical nurse at baseline and every 2 weeks (weeks 2, 4, 6 and 8). Figure 1 shows the variables collected at each assessment. The follow-up of patients in both groups will be continued until week 8 or until complete healing of the wound if this occurs earlier. A follow-up of 8 weeks was considered adequate for this study since the main action of the antioxidant dressing being evaluated is to reactivate the healing process by avoiding the excess of ROS; according to a previous study published by Castro et al. [35], a significant number of wounds improved by the fourth week. In order to promote participant retention and complete follow-up, the nurse will monitor patients in the health care centre. Furthermore, the principal investigator will have the primary responsibility for study monitoring; a formal data monitoring committee is not considered necessary because there is no access to protected information and there is no personal information recorded.

To monitor wound healing, several variables will be used: 1) wound area by direct measurement of length and width with a graduated ruler (Kundin method) [39]; 2) wound area estimated using digital photography with Helcos software [40, 41]; this software is an integrated wound management system, which allows for estimation of the wound area and the relative percentage of tissue types in the wound bed (granulation, slough and necrotic tissue); and 3) the RESVECH 2.0 scale score for chronic wound healing [37] (this scale assesses six aspects — wound size, depth/affected tissues, wound edges, type of tissue in the wound bed, exudate and infection/inflammation — with a higher score showing more improvement in the healing process from 0 (the worst possible status of the wound) to 35 points (wound healed)).

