### Outcomes

The primary outcome is the improvement in wound healing with two end points: 1) an increase in the RESVECH 2.0 scale score [37] (score at baseline minus score at 8 weeks); and 2) a reduction in the wound area (area at baseline minus area at 8 weeks). The RESVECH 2.0 score includes the assessment of the wound area, but we also decided to use the reduction in wound area as a specific end point to have a direct measurement of wound size (despite not estimating the sample size with this outcome because there were no data available from previous studies). Additionally, the values at 2, 4 and 6 weeks for each end point will be calculated. These end points are chosen for the clinical relevance of the antioxidant dressing because this product is well-known for removing the nonviable tissue (necrotic or devitalized) in the wound bed, for promoting the production of granulation tissue and for activation of the healing process [35, 42].

The secondary outcomes are the time to achieve a 50% reduction in wound area, the time elapsed until removal of nonviable tissue from the wound bed, reduction of the wound area, the number of completely healed wounds, the pain level and the area of the wound with bacterial load (clinical signs of infection or measurement of surfaces containing bacteria).

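### Follow-up stops at first complete healing, so wounds that close early have no observed week-8 value and a later reopening goes unseen

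*Protocol article*

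**What the plan says.** The stopping rule for observation appears twice in the protocol article. The Methods part of the abstract has: "Follow-up will be for a period of 8 weeks or until complete healing if this occurs earlier". Under Data collection and management it reads: "The follow-up of patients in both groups will be continued until week 8 or until complete healing of the wound if this occurs earlier".

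Under Outcomes, the two primary end points (RESVECH 2.0 score and wound area) are each the difference between the baseline and the 8-week value. Values at weeks 2, 4 and 6 are additional. The secondary outcomes include "the number of completely healed wounds".

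On who looks at the wound, the article describes two routes:

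- Data collection and management: "Each patient included in the study will be assessed by one clinical nurse at baseline and every 2 weeks". Randomization and blinding says of this nurse: "Neither the patient nor the clinical nurse is blinded to the treatment received".
- The same sentence goes on to say that pictures are coded and that "the assessor who evaluates the wound pictures and the data analyst will be blinded to the treatment". One of the listed measures is "wound area estimated using digital photography with Helcos software".

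The article does not say which of the two declares a wound completely healed. It describes no observation after closure.

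**The concern.** The end points are fixed at a calendar time, but observation ends at an event that can come earlier. For a patient whose wound closes at week 2, 4 or 6, the week-8 value has to be supplied rather than seen. The natural substitute is the value at closure, which treats closure as permanent.

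Two kinds of error then become invisible: a wound that closed and reopened before week 8, and a wound that was called closed too soon. Within each arm both push the healed count upwards, and both feed a fully healed value into the primary end points.

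The third hypothesis is a higher rate of healing with the antioxidant dressing. If that is true, more patients in that arm will leave observation early, and more of its week-8 results will rest on an unchecked closure.

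This is not a matter of detail left to a fuller document. The stop rule is stated, and it removes the data that any later analysis would need.

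**Working it through.** **The plan's own figures.** The article gives no figure for healing or reopening. Its sample size supplies the denominator used below, so I checked that first. Inputs (Sampling): 5% type 1 error, taken as two-sided; 80% power; differences of 2 points (SD 2.0) and 49.5 − 30.0 = 19.5 days (SD 20.0). The two-sample *t* calculation gives 16.7 and 17.5, so 17 and 18 per group, as stated. Allowing for 30% loss, 18 / 0.70 = 25.7, or 26 per group, against 27 stated. That is close, and nothing here depends on the difference. I use 27 per arm.

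**Observations lost under the rule.** Visits are at weeks 2, 4, 6 and 8.

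| First closure recorded at | Scheduled visits not made | Observed week-8 value |
|---|---|---|
| week 2 | 4, 6, 8 (three) | no |
| week 4 | 6, 8 (two) | no |
| week 6 | 8 (one) | no |
| week 8 | none | yes |

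**Over-counted wounds per arm.** Let *h* be the share recorded healed before week 8 and *r* the share of those that reopen by week 8. Both are assumptions. Over-count = 27 × *h* × *r*:

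| *h* | *r* = 5% | *r* = 10% | *r* = 20% |
|---|---|---|---|
| 20% | 0.27 | 0.54 | 1.08 |
| 30% | 0.41 | 0.81 | 1.62 |
| 40% | 0.54 | 1.08 | 2.16 |

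The range is about 0.3 to 2.2 wounds per arm.

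**Effect on the comparison, equal reopening rates.** Suppose 8 against 4 of 27 are called healed early (assumed).

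- As counted: (8 − 4) / 27 = 14.8 percentage points.
- 10% reopen in each arm: (7.2 − 3.6) / 27 = 13.3 points.
- 25% reopen in each arm: (6 − 3) / 27 = 11.1 points.

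The difference is overstated by 0.4 to 1 patient. The ratio stays at 2.0 throughout. If healing and reopening are both equal between arms, there is no bias in the comparison.

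**Effect if the error differs between arms.** Each wound wrongly counted in one arm only moves the difference by 1 / 27 = 3.7 points. As a what-if, take true healed shares equal at 20–40% and a 10-point excess of healed calls in one arm (0.10 × 27 = 2.7 wounds). The rejection rate of the uncorrected chi-squared test, summed exactly over the two binomial distributions, goes from 5.7%, 5.4% and 4.7% to 14.6%, 12.1% and 10.2% (at 20%, 30% and 40%). Nothing in the article shows that such an excess will occur.

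**The case against.** The best case for the plan has four parts.

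- **The rule is the same in both arms, and healing counts are secondary.** This stands. The primary end points are touched only for early healers, and only where closure did not hold or was misjudged.
- **Pictures are read blind.** This stands in part. A reader might infer that healing rests on a single look by the unblinded nurse. The article does not say so: it provides a blinded assessor of coded pictures and names nobody as the one who declares closure. That the nurse ends follow-up at the centre is plausible, but it is inference. Even so, a blinded reading of the closure photograph cannot reveal a reopening two or four weeks later.
- **A definition of healing and a confirmation step may be in the full protocol.** This also stands, and their absence from an article is not held against the plan. The point here is the stop rule, which the article does state.
- **For a time-to-event analysis, stopping at the event is normal.** That is true for time to first closure. It does not serve end points defined at week 8.

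A reader might also infer that the rule favours the antioxidant arm, or try to put a figure on the bias in mean RESVECH change. The first needs reopening or false calls to differ between arms, or a real difference in healing that is then overstated. The second needs an assumed overstatement in points for each misjudged wound. The article supports neither.

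**Conclusion.** The concern holds in a limited form. The article ends observation at first complete healing while placing both primary end points at week 8. Early closures therefore have no observed week-8 value, and a reopening or premature call before week 8 remains counted as healed. This holds whoever makes the call.

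The size is unknown, because no healing or reopening rates are given. Under the assumed rates it is of the order of one or two wounds per arm of 27. With a common reopening rate it overstates the difference slightly and leaves the ratio unchanged. A systematic advantage for one arm is possible but not shown. This is a cheap improvement worth making, not a flaw that undermines the trial.

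**What to change.** In the abstract's Methods and in Data collection and management, replace the early end of follow-up with assessment at every scheduled visit to week 8 for all patients, including those already called healed, with a coded photograph each time. Use the observed week-8 status for the primary end points and the healed count, with closure read by the existing blinded picture assessor, and say so in the text.

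Closure sustained at the next scheduled visit may be reported as a supplementary result. It should not become the definition of healing: a wound first closed at week 8 has no later visit, so that definition would drop it and favour whichever arm closes earlier.

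The article gives September 2019 as the start of recruitment and December 2020 as its expected end. A change would therefore reach later patients only. Those whose follow-up had already ended at closure should be identified as lacking an observed week-8 value.

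Cost: a wording amendment, one to three short visits for each early healer (all within the 8-week schedule), and possibly a slightly lower healed count. The change concerns observation only, not treatment.

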**Discussion:**

The findings from this study should provide scientific evidence on the efficacy of the antioxidant dressing as an alternative for the treatment of chronic wounds. This study fills some of the gaps in the existing knowledge about patients with hard-to-heal wounds.

**Trial registration:**

ClinicalTrials.gov: NCT03934671. Registered on 2 May 2019.

## Background

A wound that does not heal in the orderly stages of the healing process or does not heal within 3 months is considered a chronic wound, also known as a hard-to-heal wound or non-healing wound [1]. Hard-to-heal wounds have been defined as any wound that has not healed by 40–50% after 4 weeks of appropriate treatment [2]. Chronic wounds are a major clinical and economic problem for health care institutions because of their impact on the quality of life of both patients and caregivers [3–5]. Wound healing is impaired when the wound remains in the inflammatory stage for too long [1]. A range of factors that can delay the healing process have been described, and include the imbalance between proteases and protease inhibitors in the wound bed [6–8], bacterial colonization and the presence of biofilm [9–11], and oxidative stress [1, 4, 5, 12].

Matrix metalloproteinases (MMPs) and their inhibitors contribute to the balance between extracellular matrix degradation and deposition, creating a balance that is essential for timely and coordinated healing [7, 8]. However, in chronic wounds, the inflammatory response is augmented, and this balance becomes disrupted. This situation is characterized by elevated levels of pro-inflammatory cytokines and MMPs. Therefore, wound dressings aimed at sequestering the MMPs within the wound milieu is one particular area of interest as an alternative wound management strategy [6].

Biofilm is associated with impaired epithelialization and granulation tissue formation, and promotes a low-grade inflammatory response that interferes with wound healing [9, 10]. Over 90% of chronic wounds have an aggregation of microorganism-forming biofilm [13]. Biofilm is a survival mechanism that confers to bacteria and other microorganisms the ability to resist environmental stressors and antimicrobials due to a variety of reasons, including low metabolic activity [11].

An excess of reactive oxygen species (ROS), including singlet oxygen, hydrogen peroxide and hydroxyl radicals, causes a pro-inflammatory environment in the wound bed [14–16], attracting more inflammatory cells into the wound and creating a negative feedback loop that could delay or prevent wound closure [1, 4, 5, 17, 18]. The strong oxidizing capabilities of ROS can therefore damage many of the molecules and structures of the cells [12]. It has been proposed that the use of a dressing that can exert an antioxidant effect on wound exudates might restore the appropriate ROS balance [19].

Recently, wound management has improved significantly. New materials and bioactive wound dressings have been developed that promote a favourable environment and promote active wound healing treatment, such as collagen dressings [20, 21], MMP modulator dressings [22], and dressings with antioxidant activity of inhibitors of free radical reactions [23, 24].

Among these new advanced products, there is an antioxidant dressing (Reoxcare®) that was developed by Histocell (Bizkaia, Spain). This dressing combines an absorbent matrix obtained from locust bean gum galactomannan with antioxidant properties [25] and a hydration solution with curcumin [26, 27] and N-acetylcysteine (NAC) [28, 29]. Curcumin is a natural phenol from the rhizome of the plant *Curcuma longa* that has been used for over 2000 years as an antioxidant and an anti-inflammatory, and specifically in wounds to improve healing [30–32]. NAC is widely applied as an antioxidant molecule, and has been recently successful for the treatment of wounds [28, 33]. These three components act as free radical scavengers since two of them also have a synergistic antioxidant effect [34]. Due to the innovative design, this antioxidant dressing combines the advantages of moist healing in exudate management and free radical neutralization, achieving wound reactivation. In addition, preliminary observations suggest that this antioxidant dressing may have antibiofilm activity to eliminate and prevent reformation [24]. These findings suggest that the dressing may represent a new advanced alternative for the management of hard-to-heal wounds.

This dressing with antioxidant properties has been tested in animal models and in case series of patients with acute wounds and chronic wounds of various aetiologies (venous ulcers, neuropathic, postsurgical), pressure ulcers and neuro-ischemic diabetic foot ulcers, showing favourable results in activating the healing process [33, 35]. Data have also been published that reflect an estimate of the cost benefit of treatment with antioxidant dressings in hard-to-heal wounds with venous vascular aetiology [36]. However, there is currently no study comparing this new antioxidant dressing with standard wound dressings that maintain a moist environment that are used in routine clinical practice for the treatment of chronic wounds. This trial aims to fill this gap in the knowledge.

### Hypotheses

The hypotheses for the trial are: 1) the use of the antioxidant dressing will reduce the percentage of nonviable tissue in the wound bed more than standard wound dressings; 2) the use of the antioxidant dressing will increase new granulation tissue formation with respect to standard wound dressings; and 3) the use of the antioxidant dressing will produce a higher rate of wound healing than standard wound dressings.

### Study objectives

The primary aim of this study is to compare the effect of an antioxidant dressing on the healing of chronic wounds against the use of dressings that create a moist environment (as standard clinical practice) in patients with hard-to-heal wounds.

The secondary aims are to measure the intrapatient variation over time in the percentage of nonviable and granulation tissue in the wound bed and to measure the reduction in the wound area. Variation in the area of the wound covered by nonviable tissue is important because its reduction is an early sign of the activation in the healing process (which is an expected effect of the new dressing).

## Methods

### Design

The REOX study is a multicentre, single-blind, randomized controlled trial with parallel groups. Figure 1 presents an overview of the schedule for enrolment, intervention and assessment according to the Standard Protocol Items: Recommendations for Interventional Trials (SPIRIT) guidelines (Additional file 1).

**Fig. 1 Fig1:**
[figure not shown]
Standard Protocol Items: Recommendations for Interventional Trials (adapted from SPIRIT figure) schedule of enrolment, interventions and assessments. *MUST* malnutrition universal screening tool, *VAS* visual analogue scale

### Setting

The REOX study will run in three primary health care centres (one urban centre and two rural centres) of the Andalusian Health Service in Spain. The centres were selected taking into account that advanced practice wound nurses work in them who could participate in the study (detailed in Additional file 2).

#### Participants

Patients are eligible according the inclusion and exclusion criteria presented in Table 1*.* The sample was recruited from patients with wounds treated in one of the health care centres engaged in the study.

**Table 1 Tab1:** REOX trial inclusion and exclusion criteria

Inclusion criteria	Exclusion criteria
• Patients over 18 years of age • Patients with leg ulcers (venous, ischaemic, traumatic or diabetic foot ulcer) • Patients with dehisced surgical wounds healing by second intention • Patients with pressure ulcers • Wound area between 1 and 250 cm^2^ (wounds larger than 250 cm^2^ are very unusual and outside the scope of this kind of treatment and therefore we decided to exclude it since such a large wound could be more difficult to heal)	• Systemic inflammatory disease or oncological disease • Wounds with clinical signs of infection • Terminal situation (life expectancy less than 6 months) • Ulcers from other aetiologies: tumours, infectious • Wounds treated with negative pressure therapy • Pregnancy • History of sensitivity or allergy to any of the components of the study dressing

In addition, the following criteria for withdrawal from the study will be considered: 1) worsening of the wound according to the clinical judgment of the professional (appearance of clinical signs of infection or others); 2) appearance of allergies or hypersensitivity to the dressing; 3) death; 4) hospital admission that interrupts the treatment in the primary health care centre; and 5) change in the patient’s residence if the new residence is at a different health centre.

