### Data analysis plan

A researcher who is blinded to group allocation will perform the data analysis. All analyses will be performed with SPPS Statistics software (IBM Corp., Armonk, NY, USA). Data will be expressed as frequency and percentages for categorical variables, and mean, standard deviation, range and median for quantitative variables depending on the distribution (normality will be checked with the Shapiro–Wilk test). The statistical significance level will be set at *P* < 0.05.

For the primary outcome of improvement in wound healing the wound area reduction at 8 weeks in the intervention group compared with the standard care group will be tested by a difference of means test. The increase in RESVECH 2.0 [37] score at 8 weeks between both groups will be examined by a difference of means test (*t* test for independent groups or Mann–Whitney test depending if variables adjust to a normal distribution). The effect size will be estimated by Cohen’s *d* statistic. In addition, a repeated-measures analysis (analysis of variance or Friedman test) and a survival analysis (Kaplan–Meier) will be used to analyse the evolution over time.

For secondary outcomes, proportions and categorical variables will be tested using a chi-squared test, and continuous variables will be tested using a mean difference test (parametric or nonparametric).

Analyses will be performed between groups as randomized (an intention-to-treat analysis). Missing data for the outcomes will be tested if they are missing at random; otherwise the last observation carried forward approach will be used for imputation [43]. Furthermore, sensitivity analyses over all the completed cases (a per-protocol analysis) will be performed to check for inconsistencies.

A subgroup analysis by wound type will also be performed to explore whether the effect of the intervention differs for any type of wound according to its aetiology. Moreover, another subgroup analysis by primary care centre will be carried out to check if there are any differences in outcomes according to the centre.

No interim analyses or formal stop-study rules are planned; no harmful problems are anticipated for patients because this new dressing has been previously tested in a series of patients with wounds of various aetiologies without any serious adverse effects [35].

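### Wound worsening and hypersensitivity are grounds for leaving the study, not only for stopping the assigned dressing, so week-8 data can go missing because the patient did badly

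*Protocol article*

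**What the plan says.** Protocol article, Participants (text below Table 1): "the following criteria for withdrawal from the study will be considered: 1) worsening of the wound according to the clinical judgment of the professional". The bracketed explanation is "appearance of clinical signs of infection or others", so the trigger has no threshold and is open-ended. The second criterion is "appearance of allergies or hypersensitivity to the dressing". Death, hospital admission and a move to another health centre complete the list and are not questioned here.

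The other sections that bear on this:
- Randomization and blinding: "Neither the patient nor the clinical nurse is blinded to the treatment received". Only the assessor of the photographs and the data analyst are blinded.
- Data collection and management: one clinical nurse assesses each patient at baseline and every two weeks. "The follow-up of patients in both groups will be continued until week 8 or until complete healing of the wound", if that comes earlier. The aspects scored by RESVECH 2.0 include "type of tissue in the wound bed, exudate and infection/inflammation".
- Outcomes: both primary end points are changes from baseline to week 8. One secondary outcome is "the area of the wound with bacterial load (clinical signs of infection or measurement of surfaces containing bacteria").
- Data analysis plan: "Analyses will be performed between groups as randomized (an intention-to-treat analysis"). Last observation carried forward (LOCF) is used if the data are judged not to be missing at random. An analysis of completed cases serves as a sensitivity check.

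**The concern.** Stopping a dressing for safety or lack of benefit is proper. Ending the patient's participation for the same reason is a different matter. Under criterion 1 a patient leaves because the wound is getting worse, so whether the week-8 value exists depends on what it would have been. The trigger also overlaps with the outcomes: signs of infection are scored within RESVECH 2.0 and form part of a secondary outcome. Criterion 2 removes patients because of a reaction to the treatment itself.

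An analysis as randomised needs outcome values for the patients randomised. If values for failing patients are not collected, what remains is a comparison of patients who did well enough to stay. This matters even when the rule is applied identically in both arms: if one dressing leads to more failures, more failures are removed from that arm and the contrast is blunted.

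**Working it through.** **1. The plan's own sample size.** Inputs from Sampling: difference 2 points, SD 2.0; 49.5 against 30.0 days, SD 20.0; 5% type 1 error (two-sided assumed), 80% power, 1:1 allocation.

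The normal approximation is n = 2(1.960 + 0.842)² × SD²/difference².
- RESVECH: 2 × 7.849 × 4/4 = 15.7, so 16 per group; the exact t calculation gives 17, as stated.
- Time to 50% reduction: 2 × 7.849 × 400/380.25 = 16.5, so 17; the exact t calculation gives 18, as stated.
- Allowance for 30% loss: 18/0.70 = 25.7, so 26 per group, close to the stated 27.

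If 30% are lost, 27 × 0.70 = 18.9 remain per group, and power for 2 points is still 83% to 85% (18 or 19 per group). Numbers are therefore not the problem. The question is which patients are missing.

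**2. Is anything collected after withdrawal?** The criteria name the study as the thing withdrawn from. They stand in one list with death and relocation, and no section provides for visits afterwards. Two inferences are needed: that withdrawal ends assessment (its plain meaning), and that the professional who judges worsening is the unblinded clinical nurse (the nurse treats and assesses the patients, so this is most likely).

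**3. Size among completers.** Assumptions: RESVECH change scored so that positive means improvement, normal, SD 2.0 in each arm; control mean set to 0, since only differences matter; the lowest values are withdrawn. The withdrawn fractions are assumed or follow from an assumed threshold, because the protocol gives none.

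(a) True difference 2, one common threshold c in both arms. The mean of those who remain is μ + 2.0 × φ(a)/(1 − Φ(a)), with a = (c − μ)/2.0.

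| c | Intervention withdrawn | Intervention mean | Control withdrawn | Control mean | Difference |
|---|---|---|---|---|---|
| −2 | 2% | 2 + 2 × 0.0540/0.977 = 2.11 | 16% | 2 × 0.2420/0.841 = 0.58 | 1.54 |
| −1 | 7% | 2 + 2 × 0.1295/0.933 = 2.28 | 31% | 2 × 0.3521/0.691 = 1.02 | 1.26 |

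Differences are taken before rounding.

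(b) No true difference, worst fraction w withdrawn. The mean of those who remain rises by 2.0 × φ(z)/(1 − w), where z is the w-quantile of the standard normal.
- w = 10%: 2 × 0.1755/0.90 = 0.39
- w = 20%: 2 × 0.2800/0.80 = 0.70
- w = 30%: 2 × 0.3477/0.70 = 0.99

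Spurious difference in favour of the arm that loses more patients:
- 10% against 20%: 0.70 − 0.39 = 0.31
- 10% against 30%: 0.99 − 0.39 = 0.60
- 0% against 30%: 0.99
- equal fractions: 0

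**4. LOCF.** Let e be the mean change carried forward and r the mean change those patients would have shown at week 8, the same in both arms. The error in the difference (intervention minus control) is (w_int − w_ctl)(e − r). It vanishes only if e = r or the withdrawn fractions are equal. With two-weekly visits, the carried value may pre-date the worsening, so e can exceed r. If e − r = 2 points (an assumption) and 10% against 30% are withdrawn, the error is −0.20 × 2 = −0.40. In this example a benefit is understated; with the fractions exchanged, a harm would be.

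**The case against.** **Discretion.** The criteria are to be considered, not applied automatically, and a fuller protocol may say what happens after a dressing is stopped. A reader might infer that week-8 values are lost for every patient who does badly; the text does not support that. It does state a rule about leaving the study and contains nothing that offsets it. This limits how often values are lost; it does not remove the flaw.

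**No contradiction.** A reader might see a flat conflict with follow-up of both groups to week 8. The withdrawal list can be read as specific exceptions to a general schedule. What stands is the damage to the as-randomised analysis.

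**Unequal use by arm.** The nurse knows the allocation, so unequal use is possible, but the text does not prescribe it. Part (b) of the working shows a risk; part (a) does not need it.

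**Size.** One can construct a case in which a true difference vanishes entirely. If every non-failure gains 8 points, failures end at −4, and failure rates are 10% and 30%, the true difference is 0.20 × 12 = 2.40 and completers show 0. That zero is built in, because all non-failures are given the same gain. The arm SDs would be 12 × √(0.10 × 0.90) = 3.6 and 12 × √(0.30 × 0.70) = 5.5, against the plan's 2.0. It should not be used to describe the likely size. Withdrawal of about 30% in one arm would also use up the plan's whole allowance for loss from all causes.

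**Analysis remedies.** The completed-cases analysis is only a sensitivity check, LOCF is unbiased if the score at exit equals the eventual one, and an analysis plan could count withdrawal for worsening as failure or give it the worst rank. These points are fair, but such rules replace the missing values by assumption. They do not recover the measurements.

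**Conclusion.** The point holds as a flaw in a stated rule. Where criteria 1 and 2 are applied, the primary week-8 values are not collected for patients doing badly, missingness depends on outcome, and the planned analyses do not reliably repair it. The wording is clear; how often the rule would be used, and in which arm more, is unknown, so size and direction cannot be stated.

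Within the plan's SD of 2.0, the illustrations give a loss of roughly a quarter to over a third of a true 2-point difference among completers (2 to 1.54 or 1.26), or a spurious difference of about 0.3 to 1.0 points under unequal withdrawal. They rest on normal changes, removal of the lowest values and assumed withdrawal levels. They concern worsening only; hypersensitivity is not quantified separately. The rule should be changed, because values not collected during the trial cannot be obtained later.

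**What to change.** In the withdrawal criteria, make worsening and hypersensitivity grounds for discontinuing the assigned dressing only. Continue the scheduled two-weekly assessments and photographs to week 8 or healing, and analyse these patients in their randomised group with their observed values. Record the date and reason of each discontinuation and report them by arm. Death, admission and relocation can stay as they are.

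The cost is moderate. The visits, photographs and blinded picture assessor already exist; the case report form needs a date and a reason field. Because recruitment began in September 2019, this is an amendment during the trial, to be communicated to the relevant parties and entered in the register. Some outcomes will then be measured after a change of dressing, so the comparison becomes one of starting with each dressing.
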